### Objectives

2.2

#### Primary

2.2.1

To compare the time in days from hospital admission until surgery in the 2 groups.

#### Secondary

2.2.2

To check for difference between the 2 groups in the following variables: postoperative bleeding, medical and surgical complications, length of hospital stay, quality of life, mortality, cost-effectiveness, and cost-utility.

Agreement between the 2 different platelet function assays (see Methods) will be assessed in a subset of 20 patients.

### Participants

2.3

#### Inclusion criteria

2.3.2

Study inclusion criteria:

(1)adults (male or female) ≥ 18 years of age;(2)diagnosis of femoral fracture; and(3)receiving treatment with antiplatelet agents (acetylsalicylic acid [ASA] > 100 mg/d; triflusal > 300 mg/d; clopidogrel; prasugrel; ticagrelor; or ticlopidine) at admission to the emergency department.

Written informed consent will be obtained from all patients.

#### Exclusion criteria

2.3.3

Exclusion criteria: presence of multiple or pathological fractures, current treatment with vitamin K antagonists or new oral anticoagulants, and congenital or acquired coagulopathy.

#### Criteria for withdrawal from the clinical trial

2.3.4

The emergence of any of the following events may justify study withdrawal: severe adverse event, any clinical condition preventing the patient from continuing in the trial, protocol violations, the patient's voluntary decision to withdraw, loss to follow-up, or death.

### Outcomes and measures

2.4

#### Main outcome

2.4.1

Time, in hours, from emergency room admission until surgery.

#### Secondary outcomes

2.4.2

Clinical: postoperative bleeding, complications associated with the surgical procedure and surgical wound, medical complications during admission, perioperative mortality and mortality at 1 year, quality of life (EQ-5D-5L generic questionnaire) assessed preoperatively and postoperatively at days 5 and 30 and months 6 and 12.

Costs: length of hospital stay, surgery-associated direct health costs, laboratory tests, medications, consumables, complementary diagnostic tests, resources required to treat perioperative complications, cost associated with rehabilitation, consultations with specialists, and primary care visits after hospital discharge and during follow-up.

A subgroup analysis of 20 consecutive patients from one of the participating centers will be performed to determine the correlation between 2 platelet function systems (PlaTeLet work [PTLwork] versus the conventional Platelet Function Assay [PFA-100 system]).

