**Methods::**

Multicenter, randomized, open-label, parallel clinical trial expected to include 156 patients ≥ 18 years of age under chronic treatment with antiplatelet agents who develop a proximal femur fracture. Exclusion criteria: presence of multiple or pathological fractures, current treatment with vitamin K antagonists or new oral anticoagulants, and congenital or acquired coagulopathy.

Patients will be randomized to either

The primary endpoint is time (hours) from admission to surgery. Secondary endpoints include: platelet function; postoperative bleeding; medical-surgical complications; perioperative and 1-year mortality; quality of life; length of hospital stay; cost-effectiveness; and cost-utility. Follow-up assessments will be performed during hospital admission and at 1, 6, and 12 months after surgery.

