### Study design

2.1

Multicenter, randomized, open-label, parallel clinical trial of patients receiving chronic antiplatelet therapy admitted to the emergency department with a femoral fracture. All study participants will undergo platelet function testing and those with more than 80,000 functional platelets will be randomized to either early surgery with neuraxial anesthesia or delayed surgery with neuraxial anesthesia performed in accordance with the antiplatelet activity time of the specific antiplatelet drug (3 days for aspirin 300 mg/day and triflusal 600 mg/day; 5 days for clopidogrel and ticagrelor; 7 days for prasugrel, and 10 days for ticlopidine).

Recruitment started in September 2017 and will continue until December 2019. The last follow-up visit for the final patient included in the study will be in December 2020. To date, 81 patients have been included.

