#### Patient follow-up

2.4.3

Follow-up visits will be conducted during hospitalization, and postoperatively by phone at months 1, 6, and 12.

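### Quality of life and the 1-, 6- and 12-month follow-up are timed from surgery, whose date the allocated strategy moves, so nominally equal visits fall at different times since randomisation in the two arms

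*Protocol article*

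**What the plan says.** The abstract (Methods) states: "Follow-up assessments will be performed during hospital admission and at 1, 6, and 12 months after surgery". Section 2.4.3 agrees: "Follow-up visits will be conducted during hospitalization, and postoperatively by phone at months 1, 6, and 12". Section 2.4.2 has the EQ-5D-5L "assessed preoperatively and postoperatively at days 5 and 30 and months 6 and 12". So every scheduled assessment after the hospital stay, and every EQ-5D-5L except one preoperative value with no fixed day, is counted from the operation.

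The interval to that operation is the primary outcome (2.4.1): "Time, in hours, from emergency room admission until surgery". The strategies are designed to move it. Under 2.8.1, experimental patients above the platelet threshold are scheduled within 24 hours. Under 2.1 and 2.8.2, controls wait for the drug-specific interval, which runs from 3 days up to "7 days for prasugrel, and 10 days for ticlopidine". Section 2.7 places selection on the day of admission, with consent and randomisation following, so surgery is a post-randomisation event.

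Three other statements bear on the point:
- Mortality is listed in 2.4.2 as "perioperative mortality and mortality at 1 year", with no time origin.
- QALYs are derived from the EQ-5D-5L (2.9.2), with no start point given.
- The main efficacy analysis (2.9.2) is per protocol and takes only patients who were tested and operated on. Intention to treat, as a consistency check, keeps everyone randomised.

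**The concern.** When time zero comes after randomisation and the treatment shifts it, a comparison at the same visit label is no longer a comparison at the same time since randomisation. A control's day-5 EQ-5D-5L is taken later after the fracture than that of a cleared experimental patient. Aligning patients on time since surgery aligns them on recovery stage, so reaching that stage some days sooner earns no credit. That is one of the ways in which earlier surgery could help.

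The wait itself is represented by a single EQ-5D-5L on an unspecified day. A patient who dies or is never operated on has no postoperative visit at all, and the main analysis set removes that patient. Because controls wait longer, any such losses are expected more often among them.

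There is also a risk of mismatch in the economic analysis. Length of stay, and the costs that go with it, include the wait. The utilities behind the QALYs are collected on a surgery-based schedule. Incremental cost per QALY needs both on the same clock.

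**Working it through.** **1. The plan's own figure.** Section 2.9.1 gives SD 3.17 days, difference 1.5 days, two-sided alpha 0.05, power 0.80 and 10% loss. Per arm: 2 × (3.17 × (1.960 + 0.842) / 1.5)² = 70.1. Allowing for loss: 70.1 / 0.9 = 77.9, so 78 per arm and 156 in total, as stated. The primary endpoint already starts at admission, so this point does not change the sample size.

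**2. Offset between arms at the same visit.** Take surgery at about day 1 for a cleared experimental patient and day 3 to 10 for a control (2.1, 2.8.1). The offset is 3 − 1 = 2 to 10 − 1 = 9 days. It is smaller for experimental patients who are not cleared at once, because they also wait. The planned average difference is 1.5 days.

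| Visit | Cleared experimental, days since admission | Control, days since admission | Offset of 2–9 days as share of nominal interval | Offset of 1.5 days |
|---|---|---|---|---|
| Day 5 | 6 | 8–15 | 40–180% | 30% |
| Day 30 | 31 | 33–40 | 7–30% | 5% |
| Month 6 (about 183 days) | 184 | 186–193 | 1–5% | 0.8% |
| Month 12 (about 365 days) | 366 | 368–375 | 0.5–2.5% | 0.4% |

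**3. QALY time in the wait.** QALY = utility × days / 365.25. For 1.5 days: 1 × 1.5 / 365.25 = 0.0041 at utility 1, 0.0021 at 0.5 and 0.0008 at 0.2. The protocol gives no utilities. These are assumed values, with 1 as the ceiling.

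**4. Deaths in the wait.** The Introduction gives postoperative 30-day mortality of up to 10%. No mortality rate before surgery is given. As an assumption, apply a constant hazard with 30-day mortality m of 5% or 10%: probability of death in w days = 1 − (1 − m)^(w/30).

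| Wait w | m = 5% | Deaths in 78 | m = 10% | Deaths in 78 |
|---|---|---|---|---|
| 1.5 days | 0.26% | 0.20 | 0.53% | 0.41 |
| 3 days | 0.51% | 0.40 | 1.05% | 0.82 |
| 10 days | 1.70% | 1.32 | 3.45% | 2.69 |

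The last row would apply to a whole arm only if every control took the drug with the longest interval. No drug mix is stated, so it is an outer limit and not an estimate.

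**5. Shift of the 1-year point.** With the Introduction's 18–33% first-year mortality and a constant hazard, moving the endpoint by 1.5 days changes cumulative mortality by 0.07–0.11 percentage points. Moving it by 10 days changes it by 0.44–0.73 points.

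**The case against.** The strongest reply is that much of the plan already covers the wait. The primary outcome starts at emergency room admission. Follow-up visits also run during hospitalisation, complications include "medical complications during admission", length of stay is collected, and the cost-effectiveness measure runs from admission to first mobilisation. The intention-to-treat set keeps unoperated patients. Section 3 describes the analysis of morbidity and mortality as exploratory. All of this stands, and it limits what is at risk.

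A reader might infer that deaths during the wait fall outside the mortality outcome. The documents do not say so. One-year mortality has no stated origin, and a visit schedule is not a mortality clock. What would drop such deaths is the surgery requirement in the main per-protocol set.

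A reader might also infer that QALYs begin at surgery. The start point is not stated, and the preoperative EQ-5D-5L could be used to value the wait.

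A third tempting reading is that the schedule removes the benefit of earlier surgery altogether. It does not. If delay leads to complications, death or lasting loss of function, these remain visible at day 30 and at 6 and 12 months. Nor is this immortal time in the usual sense: a clock starting at surgery does not credit the waiting period to anyone. The possible problem is selection, through the loss of patients who never reach surgery.

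The objection does not remove the stated rule itself. Quality of life and later follow-up are anchored to an event whose date depends on the arm.

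**Conclusion.** The point holds in a limited form. The assessment schedule uses an arm-dependent time origin by stated rule, and the origin for 1-year mortality and QALYs is left open. The effect is material for the day-5 and day-30 EQ-5D-5L and minor at 6 and 12 months. Only the part of the benefit that arises from the shorter wait itself is at risk.

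In size it is modest: at most 0.004 QALY per patient and about 0.2–0.4 deaths per arm of 78 at the planned 1.5-day difference, and about 0.4–0.8 deaths for a 3-day wait. The death figures rest on a constant hazard, on an assumed 5–10% 30-day mortality, and on carrying a postoperative rate back to the period before surgery. The QALY figure is a ceiling at full health. The primary comparison and the 156 patients are untouched. The correction is worth making because it is cheap and removes an avoidable bias.

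**What to change.** In 2.4.2, 2.4.3 and 2.9.2:

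- Set time zero at randomisation (the day of admission) for 1-year mortality, costs and QALYs.
- Analyse these in all randomised patients, and count every death from time zero, including deaths before surgery.
- Build the QALY area from actual assessment dates, with the preoperative EQ-5D-5L covering the wait, so that costs and utilities share one origin.
- Keep the postoperative day-5 EQ-5D-5L, and the day-30 one for patients already enrolled, as recovery measures reported at their true dates.

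Treatment, sample size and primary endpoint do not change. The cost is a little extra analysis work. Section 2.7 already names admission and surgery dates and times among the key variables. Dates of death are not named there, so it should be confirmed that they are recorded.

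Re-dating the later calls for new patients is optional. With 81 patients already included (2.1), it would mix two schedules within each arm. Analysing by actual dates handles that, but day-30 values already collected cannot be moved.

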#### Patient follow-up

2.4.3

Follow-up visits will be conducted during hospitalization, and postoperatively by phone at months 1, 6, and 12.

### Randomization and allocation of interventions

2.5

A computer-generated permuted block randomization sequence, stratified by center, will be used for the randomization process. A web-based platform (www.clipnasis.com) will be used to allocate patients to the interventions. This platform will randomly assign a number to each patient and to the corresponding intervention. Researchers will be blinded to the allocation sequence of the study interventions.

### Blinding

2.6

Necessarily, the patients and researchers will know which intervention they have been allocated. However, to avoid influencing the timing of the surgical procedure, the investigators will be blinded to the platelet function status in the control group.

### Implementation and data collection

2.7

Figure 1 describes the patient recruitment process and the study plan. A competitive recruitment process will be used; thus, no predetermined limit to the total number of patients per center has been established. Patient selection will be performed on the day of admission to the hospital emergency department. Researchers will first verify that the patient meets the study inclusion criteria. The patient will then be informed about the clinical trial and asked to participate. Patients who agree to participate will be enrolled in the study after signing the informed consent form. Next, they will be randomized to one of the 2 study groups.

**Figure 1 F1:**
[figure not shown]
Flowchart of the clinical trial.

Blood samples will be taken at the time points established in the study and analyzed in the laboratory within 10 minutes of extraction to determine platelet function. Platelet function will be performed in all patients using the PFA-100 system (Siemens, Munich, Germany). This system is based on the adhesion properties of platelets when subjected to stress conditions and in the presence of a particular agonist. The citrated whole blood is conducted through a capillary to a collagen membrane with a microscopic opening (147 μm) covered by an agonist (adenosine diphosphate [ADP] or epinephrine). The system determines the time it takes for the hole to close (closure time).

In a small subset of patients (n = 20), the PTLwork system (Helena Laboratories, Beaumont, TX) will also be used to determine preoperative platelet function. This 2-step system determines the number of platelets added and/or inhibited. In the first step, the total platelets are counted in a blood sample. Next, a second sample containing a platelet agonist (ADP or collagen) is examined to count the number of non-functional platelets. The difference between the 2 platelet counts yields the number of functioning platelets.^[23]^

The key outcome variables of this clinical trial (date and time of admission; date and time of surgery; blood loss; transfusion units; and complications) will be obtained from patient medical records and by direct patient interview (in person and/or by telephone).

The collected information will be uploaded to a password-protected electronic web-based database (http://www.clinapsis.com).

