#### Experimental intervention

2.8.1

At emergency room admission, the antiplatelet medication will be discontinued and platelet function will be determined. In patients with >80,000 functional platelets, the surgery will be scheduled within the next 24 hours. However, if the level of functional platelets is <80,000, then the platelet assay will be performed once per day for the next 2 days or until normalized (whichever occurs first): surgery will be performed within 24 hours after normalization. If the number of functional platelets has not normalized after 3 days, surgery with neuraxial anesthesia will be scheduled in accordance to the margin of safety time established for the specific antiplatelet medication.

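### The rule for early surgery is a count of functional platelets, but the assay assigned to all patients reports a closure time

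*Protocol article*

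**What the plan says.** **The rule.** Section 2.8.1 (experimental intervention): "In patients with >80,000 functional platelets, the surgery will be scheduled within the next 24 hours". Otherwise, "if the level of functional platelets is <80,000, then the platelet assay will be performed once per day", for up to two more days or until normal. Section 2.1 (study design) uses the same number as an entry condition: "those with more than 80,000 functional platelets will be randomized".

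**The assay for everyone.** Section 2.7 (implementation and data collection): "Platelet function will be performed in all patients using the PFA-100 system". Its output is then described: "The system determines the time it takes for the hole to close (closure time").

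**The assay for a few.** Section 2.7 continues: "In a small subset of patients (n = 20), the PTLwork system" is used as well. Of this second system it says: "The difference between the 2 platelet counts yields the number of functioning platelets". Section 2.4.2 places these 20 patients, taken consecutively, at a single centre and gives the purpose as comparing the two systems.

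**The control arm.** Under section 2.8.2, surgery is timed by the safety interval of the drug. Platelet function is measured the day before surgery and withheld from the researchers, so it decides nothing in that arm.

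**The concern.** A closure time cannot be compared with 80,000 platelets. The text cannot presume a conversion either, because agreement between the two systems is itself a secondary objective (section 2.2.2).

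Three things depend on the rule:

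- **The intervention.** The trial tests surgery timed by platelet function. This rule sets the timing, and so the primary outcome, in the experimental arm.
- **Safety.** The rule clears patients for spinal anesthesia before the drug's waiting time has passed. The Introduction calls knowing the number of functional platelets crucial for doing this safely, and the Discussion treats neuraxial anesthesia as contraindicated when early surgery is indicated but platelet function is unknown.
- **The main analysis set.** Section 2.9.2 makes per protocol the main analysis and requires that the patient had the corresponding platelet test. Which test that is stays unclear while the conflict stands.

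**Working it through.** **1. Units side by side**

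| Section | Role | Unit |
|---|---|---|
| 2.1 | condition for randomization | count, above 80,000 |
| 2.8.1 | surgery within 24 hours, or retest | count, above or below 80,000 |
| 2.7, PFA-100 | all patients | closure time |
| 2.7, PTLwork | 20 patients, in addition | count |

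The rule and the universal assay are in different units. The article gives neither a closure-time cut-off nor a conversion.

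**2. The denominators**

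Section 2.9.1 gives SD 3.17 days, difference 1.5 days, two-sided alpha 0.05, power 0.80 and 10% loss. By the normal approximation:

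n per arm = 2 × (3.17 × (1.960 + 0.842) / 1.5)² = 70.1

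70.1 / 0.90 = 77.9, so 78 per arm and 156 in total.

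This reproduces the stated sample size, which the concern does not touch.

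**3. Patients with no result in the unit of the rule, read literally**

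At most 20 patients have PTLwork. Placing all 20 in the group being counted gives a lower bound for each:

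- All patients: 156 − 20 = 136; 136/156 = 87%.
- Experimental arm: 78 − 20 = 58; 58/78 = 74%. With an even split of the 20 (an assumption), 78 − 10 = 68; 68/78 = 87%.
- Already included (81, section 2.1): 81 − 20 = 61; 61/81 = 75%.

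**4. Which arms are affected**

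This depends on which text holds. If section 2.1 is followed, the count gates entry and both arms are affected. Section 2.7, however, goes from consent straight to allocation: "Next, they will be randomized to one of the 2 study groups". Section 2.8.1 also keeps experimental patients below 80,000 in the trial and retests them. On that reading only experimental-arm timing is affected, because controls are timed by drug.

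**The case against.** The strongest reply is that only section 2.7 limits PTLwork to 20 patients. Sections 2.2.2 and 2.4.2 say just that the two assays are compared in 20 patients, which fits either one being universal. Sections 2.1 and 2.8.1 need a count, which only PTLwork is said to provide. The simplest explanation would then be that the two names were exchanged in section 2.7, with PTLwork and 80,000 as the real rule. This is plausible, but the article does not settle it: section 2.4.2 calls PFA-100 the conventional system, and section 2.7 describes each device under its own name and output.

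It can also be said that the article condenses a fuller protocol and that Figure 1 is not shown, so a closure-time cut-off may exist there. That is so, and the absence of a cut-off is not the point. Such a cut-off would not make the printed threshold and the printed assay consistent.

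Two objections limit the size. The 136 of 156 includes controls, whose result decides nothing unless the count gates entry; 58 of 78 is the figure that bears on the rule in section 2.8.1. The conflict between gating entry by the count and randomizing straight after consent is also a separate matter, and most of the text weighs against the gate. Both points stand.

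Finally, the sample size is unaffected, as is the recording of admission and surgery times, and randomized arms can be compared whichever assay triggered surgery. That is right, but the strategy still could not be reproduced, nor its safety judged, from the text as printed.

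**Conclusion.** The concern holds. The stated threshold and the stated assay contradict each other, and no part of the article reconciles them. Read literally, at least 74% of the experimental arm has no result in the unit of the rule that decides early surgery. The corresponding lower bounds are 87% of all patients and 75% of those already included.

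These figures assume that the PTLwork subset is 20 patients, as section 2.7 says, and that the planned arm sizes are met. They are consequences of the text and do not show how the trial was run; section 2.8.1 itself implies a count in every experimental patient. The contradiction must be corrected because it concerns the definition of the intervention and the clearance for spinal anesthesia.

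**What to change.** Correct sections 2.1, 2.7 and 2.8.1 so that one named assay drives the decision, with the threshold in that assay's unit:

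- if the names were swapped in section 2.7, PTLwork for the decision with 80,000, and PFA-100 as the comparison in the 20 patients; or
- if PFA-100 really decides, a stated closure-time cut-off in place of 80,000.

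The clinical team must say which text is right. In either case, state which assay and cut-off were used for the 81 patients already included.

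If only the wording is wrong, the cost is low: a correction to three sections and no new procedure. If the deciding assay itself has to change, that is a substantive amendment, and patients before and after it must be identified in the analysis.
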